## Abstract

**Introduction::**

High-intensity interval training (HIIT) programs have demonstrated positive effects on cardiorespiratory fitness and cardiometabolic parameters, but their impact on other health parameters (such as body mass and fat) and cognition remains unclear. This paper presents the rationale and methods of a HIIT after-school physical activity (PA) intervention (MOVI-daFIT!) on reducing fat mass and cardiovascular risk, and improving physical fitness, executive function, and academic achievement among children aged 9 to 11 years old.

**Methods::**

A cluster randomized controlled trial (RCT), including 10 schools from Cuenca province, Spain, was designed. Schools were randomly assigned to the MOVI-daFIT! intervention and to the control group. Children were evaluated at the beginning (September 2017) and at the end (June 2018) of the school year. Children in the intervention group were involved in 60-minute after-school sessions 4 days per week developed in the school setting. Each session consisted of 15 minutes of set-up and warm-up games, 28 minutes of games using the HIIT protocol, and 10 minutes of cool down. In addition, children in the intervention and control groups received 2 regular 50-minute physical education sessions per week, as it is compulsory by law in Spanish schools.

**Conclusion::**

This study will determine the effect of an after-school physical activity intervention (MOVI-daFIT!), designed as a HIIT program, on reducing fat mass and cardiovascular risk, and improving fitness and cognition, including executive function and academic achievement.

## Introduction

1

During the last decades, children's sedentary behaviors have been continuously increasing.^[1,2]^ As the World Health Organization (WHO) reports, 81% of adolescents do not meet the recommended 60 minutes per day of moderate-to-vigorous intensity physical activity.^[3]^ Children have reduced the time spent on physical activity within the school setting, where academic subjects other than physical education have been progressively gaining importance^[4]^; furthermore, screen-based activities have replaced most time spent for leisure physical activity.^[2]^ In contrast, growing scientific evidence recommends increasing physical activity time to achieve benefits on children's health by counteracting the consequences of sedentary behaviors.^[5]^

Physical inactivity is one of the leading factors contributing to the worldwide increase of overweight/obesity rates.^[6]^ In addition, the increase of children's physical inactivity rates is coupled with a decrease in their cardiorespiratory fitness levels.^[7]^ Both overweight/obesity and low levels of fitness are associated with not only children's physical health disorders such as hypercholesterolemia, hypertension, hyperinsulinemia, and worsening subclinical arteriosclerosis markers,^[8–13]^ but also low scoring on cognition, academic achievement, self-esteem, and health-related quality of life.^[14,15]^

Because children spend a lot of time in school, this has been proposed as a good setting to promote healthy habits that decline the negative consequences of physical inactivity.^[16]^ The school environment offers a permanent platform to access people at early ages, a key period of biological and social life in which physical activity interventions could produce positive short- and long-term benefits, and behavioral changes that tend to persist from infancy through adolescence to adulthood.^[5]^ School-based physical activity interventions have demonstrated positive effects to reduce body fat and cardiovascular risk factors.^[17]^ Furthermore, benefits of physical activity programs on children's cognition, metacognition, and academic performance have been reported.^[18,19]^

Most of the previous interventions were aimed at achieving international recommendations for physical activity. With this aim, in recent years high-intensity interval training (HIIT) programs have been implemented, which have demonstrated to be time-efficient and to easily fit into children's patterns of spontaneous exercise.^[20]^ HIIT programs have reported greater positive effects than other physical activity programs on cardiorespiratory fitness and cardiometabolic parameters, and are particularly effective in lowering blood pressure and cardiovascular disease biomarkers.^[20,21]^ However, their impact on other health parameters, such as body mass and fat, and cognition, remains unclear.

## Aims

2

The purpose of this paper is to describe the study design and protocol for a HIIT physical activity school-based program named MOVI-daFIT!. The objective of this study was to assess the effectiveness of the MOVI-daFIT! intervention in children from 9 to 11 years old on improving physical fitness, and reducing fat mass and cardiovascular risk; and improving executive function and academic achievement.

## Methods

3

### Design

3.1

This study was designed as a cluster randomized controlled trial with 2 parallel groups. The CONSORT 2010 statement: extension for cluster trials^[22]^ will be used to conduct and report results of this trial.

### Recruitment and allocation

3.2

The Clinical Research Ethics Committee of the ‘Virgen de la Luz’ Hospital in Cuenca approved the study protocol. The development of this project was supported by the Department of Education and Science of the Junta de Communities of Castilla-La Mancha (Spain), which sent a letter informing each school that agreed to participate about the study. After that MOVI-daFIT! researchers provided information about the objectives and methods of the study to the head teacher, the school board, and the physical education teachers of the schools. The consent of the School Council, board of community participating in school management, was required to participate in MOVI-daFIT!. Finally, 10 schools from 10 towns in the province in Cuenca, Spain, agreed to participate (Fig. 1).

**Figure 1 F1:**
[figure not shown]
Flow chart of trial participants. CG = control group; IG = intervention group.

After approval from School Councils, the schools were randomly assigned to either the intervention group (IG) or the control group (CG), by using the statistical package StatsDirect.

### Participants and study sites

3.3

In all schools, all children belonging to the fourth and fifth grades of primary school (9–11 years old) were invited to participate. Parents were invited to a meeting in which researchers provided complete information about the objectives and procedures of the study. Signed informed consent from parents was compulsory for the children whose parents decided that they will participate in MOVI-daFIT!. Parents were encouraged to take children's opinion into consideration for this decision.

Children's clinical parameters information was sent to their parents after each measurement. In addition, appropriate recommendations were suggested when abnormal values were detected. Finally, parents had access to the MOVI website (www.movidavida.org), where they could post any questions to the MOVI group and share videos or photos.

### Inclusion and exclusion criteria

3.4

To participate in the study, schools were required to have at least one full classroom of fourth grade and another of fifth grade. Children were excluded when presenting Spanish learning difficulties; teachers or parents reported any child's serious physical or mental disorders which could impede participation in the activities of the program; or pediatricians reported any child's chronic disorder such as heart disease, diabetes, or asthma that could prevent participation in the activities of the program.

### Intervention

3.5

#### MOVI-daFIT!: description

3.5.1

This program includes recreational and noncompetitive physical activities, based on traditional games, but using a HIIT protocol adapted to children's age. A detailed description of the playground games used in the exercise sessions is freely accessible at www.movidavida.org. The same games as the MOVI study were used, but several adaptations to increase physical intensity were made. For example, in a game of chase when a child is caught, he/she cannot stand still waiting for another child to save him/her but must do jumping jacks, running on the spot, squats, and so on. An example session can be found in Table 1.

**Table 1 T1:**
[figure not shown]
MOVI-daFIT! session type.

The program was implemented from October 2017 to May 2018, including a total of 102 sessions in each school. For statistical analyses, children who attended ≥80% of the MOVI-daFIT! sessions were considered to have received the intervention.

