### Analyses of outcomes

5.2

After measurements, participants’ data will be entered into a database by 2 independent researchers. Blinding on handling data will be assured by separating measurements values from general participant's information. Statistical analyses will be performed in 3 waves. First, the effectiveness of the randomization processes will be checked by exploring outlier values, and the normal distribution of the variables using the Kolmogorov Smirnov test and graphical procedures (normal distribution plots). After checking the truthfulness of outliers and extreme values, these will be winsorized using the 1st percentile and 99th percentile of the distribution of variables. Before conducting the analyses, and after considering the missing at random or missing completely at random nature, children with missing data will be imputed using chained equations.

Second, mixed regression models^[44]^ will be used to assess the change between the baseline and final variable measurements. For these analyses, each variable will be considered as an independent variable, and the intervention as a fixed effect. In addition, the analyses will be adjusted for baseline data, age, sex, and school (cluster).

Finally, the previous analyses will be done using propensity score methods for comparing the IG and the CG in the scenario in which IG subjects have the same characteristics as the CG ones at the baseline. This statistical method allows each child in the IG to be matched with a child in the CG, by using a variable as reference.

Results will be considered statistically significant at *P* < 0.05. The analyses will be performed using version 9.2 of STATA14. Finally, statisticians conducting the analyses will be blinded to the participant's allocation.

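### The 80% attendance rule, read with an undefined intervention term in section 5.2, lets a post-randomisation filter present in one arm only decide who counts as treated

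*Protocol article*

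**What the plan says.** Section 3.1 describes a "cluster randomized controlled trial with 2 parallel groups". Under section 3.2, "10 schools from 10 towns in the province in Cuenca, Spain, agreed to participate", and the labels intervention group (IG) and control group (CG) are introduced as the arms to which those schools were randomly assigned.

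Section 3.5.1 describes the programme, "including a total of 102 sessions in each school", and then sets a rule expressly for the statistical analyses: children present at 80% or more "of the MOVI-daFIT! sessions were considered to have received the intervention".

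Section 5.2 specifies mixed regression models in which "each variable will be considered as an independent variable, and the intervention as a fixed effect", adjusted for baseline, age, sex and school. A further step repeats the analysis with propensity-score matching of IG children to CG children. Chained-equation imputation is planned for missing data. Section 5.2 does not mention the attendance threshold, does not define the intervention term as the randomised arm, and does not confine the section 3.5.1 rule to a secondary analysis.

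**The concern.** The sentence in section 3.5.1 is framed as a rule for the analyses, not as a description of adherence. Adherence has its own place in section 3.5.4, where small gifts are tied to the same threshold. It is the article's only statement of who counts as having received the intervention, and the intervention is the term that section 5.2 puts in the model.

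If the rule is followed, intervention-school children must clear a filter that control children never face. Keeping up four high-intensity sessions a week from October to May plausibly reflects motivation, fitness and family support. These may predict change in fitness, fat, cognition or grades whether or not the programme works. The estimate would then mix the programme's effect with the prognosis of regular attenders. It would also no longer answer the question in the Aims section, which is the effectiveness of the programme in the children of these schools.

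**Working it through.** The article gives no figure for this point, so there is none to reproduce. The check has two parts.

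**The cut-off.** 0.80 × 102 = 81.6, so a child needs 82 sessions. A child with 81 sessions (81/102 = 79.4%) would not count as having received the intervention.

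**The possible size of the bias with no true effect.** The inputs are all assumptions:
- c, the share of intervention-school children reaching the cut-off: 0.5 to 0.9.
- r, the correlation of attendance with outcome change for reasons unrelated to the programme: 0.1 to 0.3.
- Attendance propensity is normal, outcome change has SD 1, the arms are of equal size, and clustering and covariate adjustment are ignored.

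Let z be the normal cut-point with a share c above it, and φ(z) the normal density there. Attenders have mean propensity φ(z)/c and non-attenders −φ(z)/(1 − c).

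- If children below the cut-off are dropped: bias = r × φ(z)/c.
- If they are counted with the controls, they form a share (1 − c)/(2 − c) of that pool: bias = r × [φ(z)/c + φ(z)/(2 − c)].
- If they stay in the intervention arm: bias = 0.

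Worked example, c = 0.8 and r = 0.2: φ(z) = 0.280. Dropped: 0.2 × 0.280/0.8 = 0.070. Counted as control: 0.2 × (0.280/0.8 + 0.280/1.2) = 0.117.

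| c | Dropped: r = 0.1 | r = 0.2 | r = 0.3 | Counted as control: r = 0.1 | r = 0.2 | r = 0.3 |
|---|---|---|---|---|---|---|
| 0.9 | 0.019 | 0.039 | 0.058 | 0.035 | 0.071 | 0.106 |
| 0.8 | 0.035 | 0.070 | 0.105 | 0.058 | 0.117 | 0.175 |
| 0.7 | 0.050 | 0.099 | 0.149 | 0.076 | 0.153 | 0.229 |
| 0.6 | 0.064 | 0.129 | 0.193 | 0.092 | 0.184 | 0.276 |
| 0.5 | 0.080 | 0.160 | 0.239 | 0.106 | 0.213 | 0.319 |

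Section 5.1 plans on a difference of 0.3 in cardiorespiratory fitness, with no unit. If that is in SD units, the worked example amounts to 0.070/0.3 = 23% or 0.117/0.3 = 39% of the planning effect.

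Two cautions apply. Adjustment for baseline lowers r to whatever correlation remains after it, so the adjusted bias would be smaller than tabulated. And if the programme does work, counting partly exposed children as controls pulls the estimate the other way. No false-positive rate is given, because it would need the intraclass correlation, which the article does not report.

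**The case against.** The strongest reply is that the article keeps the randomised arms as its comparison. Section 3.2 ties IG and CG to the school allocation. Section 5.1 sizes the trial on a difference between IG and CG, and section 5.2 speaks of comparing them. Nowhere is IG redefined as attenders only. Imputing missing data leans towards keeping children in. The 80% sentence sits in the programme description, and could simply define adherence for a per-protocol analysis. This stands in part: an as-randomised reading is open, so the article cannot be said to have replaced the randomised comparison. It does not dispose of the point. The sentence says that it is for the statistical analyses, and nothing in section 5.2 limits it or says that children below 80% stay in the IG.

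A second reply is that analysis sets are commonly left to a fuller protocol or analysis plan. That is right, and the lack of an intention-to-treat statement is not the point here. The point is a rule that the article does state and that would bias a school-randomised comparison if followed.

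A third is that baseline adjustment and propensity matching deal with attenders being fitter or leaner at the start. They deal with part of that. They do not remove selection on unmeasured motivation or family support, and imputation concerns missing values, not non-attendance.

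A reader might also infer a breach of blinding, since attendance exists only in intervention schools and section 5.2 says that "statisticians conducting the analyses will be blinded to the participant's allocation". The article does not support this. Section 3.5.4 has the monitors supplying attendance information, and nothing says that it reaches the statisticians.

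**Conclusion.** The concern holds as a badly fixed rule. Sections 3.5.1 and 5.2 together let a post-randomisation filter, present in one arm only, define the treatment term, and the handling of intervention-school children below 80% is not stated. A reader might go further and conclude that the main analysis is by compliance instead of by randomised school. The article does not say so, and its IG and CG wording leaves room for the opposite.

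If the rule is applied by dropping these children or counting them as untreated, the illustrative bias with no true effect is about 0.02 to 0.32 SD before covariate adjustment. It would be zero if every child is kept in the school's arm, or if attendance is unrelated to outcome change. The attendance share, the correlation and the SD units are all assumed, so the range shows what could be at stake and does not estimate what will happen. A bias towards benefit is likely but not proven.

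**What to change.** In section 5.2, state that the primary analysis includes every consented child in the arm to which the child's school was randomised, regardless of attendance, and that the intervention term in the mixed models is that randomised arm. In section 3.5.1, limit the 80% rule to a supplementary analysis labelled as such, either per-protocol or complier-average with school allocation as the instrument. Its assumptions should be stated; a complier-average estimate at a cut-off, for example, takes attendance below it to have no effect.

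The cost is some wording and one extra model. No new data are needed, since attendance is already reported under section 3.5.4. The downside is that the headline effect may be smaller, because children who attended little stay in the intervention arm.

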#### MOVI-daFIT!: prescribed amount/intensity

3.5.2

Children were involved in 60-minute after-school sessions 4 times a week developed within the school setting.^[23]^ Each session consisted of 15 minutes of set-up and warm-up games, followed by 28 minutes of games using the HIIT protocol, in which a 4-minute game of high-intensity activity (at 85%–90% of the maximum heart rate, approximately 178–190 ppm) was followed by a game of recovery activity lasting 3 minutes (at 65%–75% of the maximum heart rate, approximately 136–147 ppm), and this sequence was repeated 4 times. Finally, children played a 10-minute low-intensity game for cool down (Fig. 2). Sometimes, the games were repeated to minimize the time spent explaining. To ensure that children reached the intensity of the planned physical activity, children's heart rates were randomly monitored each session. When the planned intensity per session was not reached, trainers modified the exercise characteristics to achieve the daily target (increasing the number of children catching, reducing the playing space or including new rules). On the contrary, if the children exceeded the desired intensity, there was no recovery game, and children rested standing while listening to the explanations for the next game.

**Figure 2 F2:**
[figure not shown]
Session design MOVI-daFIT!.

To increase the workload, after the 12th week of the program, the session's protocol increased the HIIT time to 32 minutes, which included 4 blocks of alternating 5 minutes of high-intensity activity with 3 minutes of recovery activity. During this phase, the warm-up and the cool down lasted approximately 10 minutes each. This volume and intensity were maintained until the end of the program.

#### MOVI-daFIT!: design and teacher training

3.5.3

The MOVI-daFIT! program was designed by 2 physical activity and sport sciences graduates, and implemented by trainers with technical qualifications in physical activity and sports who were blinded to the participants group assignment. Trainers learned the MOVI-daFIT! program during a 1-day training session to standardize the implementation of the program. The workshop was conducted by the main researcher of the project and the researchers responsible for the design of the physical activity program. The main objective was to engage, inspire, and equip trainers with the necessary skills to perform the MOVI-daFIT! protocol.

#### MOVI-daFIT!: monitoring and adherence

3.5.4

To improve adherence to the program, participants attending ≥80% of the sessions received small gifts depicting the logo of the program's mascot as a reward (t-shirts, fidget spinners, etc.). A telephone number and an email address were available for parents and teachers to keep them informed about the development of the program. Monthly contacts with monitors were held by phone and e-mail to obtain information on the attendance of children to the program. Moreover, a visit to the schools was made to assess program performance and conduct satisfaction surveys with children. Finally, the monitors were responsible for accounting adverse effects derived from the program and recording the reasons for dropout.

Children in both the IG and CG received, as it is compulsory by law in Spanish schools, 2 regular 50-minute physical education sessions per week.

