**Table 2 T2:**
[figure not shown]
Study variables.

The measurements were made at school by evaluators who were previously trained to standardize the measurements and blinded to the group in which participants were allocated.

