### Sample size

5.1

The sample size was estimated by considering a 0.3 difference mean change between the IG and the CG in cardiorespiratory fitness, as has been reported in previous studies.^[42]^ The estimates were calculated considering an alpha error of 0.05 and statistical power of 0.80. In addition, a mean of 40 children was considered in each classroom with a 15% dropout rate. For sample size calculation, optimal design software was used and Donner and Klar's models were considered.^[43]^

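### Harms are limited to effects attributed to the programme and counted by its monitors, so the stated rule allows no between-arm comparison of injury or illness

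*Protocol article*

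**What the plan says.** The article deals with harms and with the recording of dropout reasons in one sentence, in section 3.5.4 on monitoring and adherence: "the monitors were responsible for accounting adverse effects derived from the program and recording the reasons for dropout". The attribution limit in it applies to adverse effects. Dropout reasons carry no such limit, and the sentence does not say whether dropout means leaving the programme or leaving the study, or in which arm.

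The monitors are not defined, but the same section ties them to the programme: "Monthly contacts with monitors were held by phone and e-mail to obtain information on the attendance of children to the program". It then describes what both arms have in common: "Children in both the IG and CG received, as it is compulsory by law in Spanish schools, 2 regular 50-minute physical education sessions per week". The control arm is given nothing beyond this.

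The staff who see children in both arms are the assessors, described under Outcome measures as "evaluators who were previously trained to standardize the measurements and blinded to the group in which participants were allocated". The text gives them no task on harms or dropout. On missing data, section 5.2 plans imputation by chained equations "after considering the missing at random or missing completely at random nature", without distinguishing the arms.

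**The concern.** A harms rule should let the trial compare what happened to children allocated to the programme with what happened to those who were not. Children of this age are injured and fall ill anyway, so the question is whether four extra sessions a week change the frequency. A rule that admits only events thought to be caused by the programme cannot answer it, and a low count is easily read as evidence of safety.

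The point at which attribution is made also matters. If it is a condition for entering an event, then an injury noticed later at home or in a physical education class may never be written down, and no later analysis can recover it or judge its cause again.

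Dropout reasons are a lesser matter. They help in judging whether missing data are plausibly missing at random, and they help most when collected in the same way in both arms. The article places their recording with programme monitors, under a programme heading, and is silent on control schools.

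**Working it through.** The article states no adverse-event rate, total sample size or allocation ratio, so there is no figure of its own to reproduce. The check on harms is one of logic, and arithmetic serves only to scale the dropout question.

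**Harms.** Let I and C be all injuries and illnesses of interest in the intervention and control arms, and A the part of I that is attributed to the programme when recorded, so A ≤ I. Let n₁ and n₀ be the numbers of children in the two arms.

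- Contrast wanted: I/n₁ − C/n₀. It may be positive, zero or negative.
- Contrast available under the rule: A/n₁ − 0. The control term is zero because section 3.5.4 gives control children only their ordinary physical education, so there is no programme to which an event could be attributed.
- Available minus wanted: C/n₀ − (I − A)/n₁.

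The gap depends on C and on I − A, the two quantities that the rule does not collect. Its sign and size are therefore unknown. The available contrast can never be negative, so the rule could not show a reduction in injury or illness even if there were one. None of this requires an assumption about who works in control schools.

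**Who counts.** Section 3.5.4 makes the monitors responsible and links them to programme attendance. The assessors who see both arms have no stated harms task. No step is described in which someone else judges relatedness.

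**Dropout reasons.** The inputs are the sample size section's "a mean of 40 children was considered in each classroom with a 15% dropout rate", the 10 schools in section 3.2, and an assumed 1:1 allocation of children. Expected control dropouts = (total ÷ 2) × 0.15:

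| Assumed total | Basis | Control dropouts |
|---|---|---|
| 400 | 10 schools × 40 | 200 × 0.15 = 30 |
| 500 | size of the accelerometer subsample | 250 × 0.15 = 37.5, about 38 |
| 800 | 10 schools × 2 classrooms × 40 | 400 × 0.15 = 60 |

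The first row fits poorly with a subsample of 500, which implies at least that many children, so the upper part of the range is more plausible. The table shows how many control children the silence concerns. It does not show that their reasons went unrecorded.

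**The case against.** The strongest reply is that this is a condensed article and that section 3.5.4 describes the intervention, so control-arm procedures would not be expected there. That stands against several stronger readings that a reader might infer:

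- *Monitors are the only source, and nothing is recorded in control schools.* The article makes monitors responsible; it does not exclude other sources. The flow chart and the table of variables could not be seen.
- *Control dropouts have no recorded reason.* The article does not say so. It is silent, and the full protocol may cover the point.
- *Missing at random cannot be judged for control children.* This does not follow. The assumption is conditional on observed data, and completers and non-completers can be compared on the extensive baseline measures in both arms.
- *The people counting are unblinded.* The article does not state this of the monitors. Section 3.5.3 says the programme was "implemented by trainers with technical qualifications in physical activity and sports who were blinded to the participants group assignment". That is hard to picture for staff who run the sessions, and the article never says whether monitors and trainers are the same people.
- *Adverse effects cannot reach the investigators during the school year.* The stated purpose of the monthly contact is attendance, but the article also describes a school visit, a telephone number and e-mail address for parents and teachers, and a website for parents' questions. None is labelled a route for harms, but none is closed to them.

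It is also fair to say that safety is not among the stated aims and that no planned effect analysis depends on this sentence.

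The reply does not remove the core. On harms the article is not silent: it states what is counted and by whom, and that scope is one-armed by its own wording. An analysis plan cannot restore events that the collection rule left out.

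**Conclusion.** The point holds for harms. As written, the rule gives a programme-attributed count in the intervention arm and no control comparison, and it loses events that are not attributed when recorded. This rests on the wording of section 3.5.4 and on the control arm receiving no programme. It also takes the monitors to be attached to the programme, which is a fair reading of their attendance reports although the article does not define them.

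For dropout reasons only a weaker statement is supported: the article does not say how they are recorded in control schools, and like-for-like collection would strengthen the missing-data judgement without being required for it. The range of about 30 to 60 control children depends on the assumed total and on equal allocation.

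The consequence is moderate. Any safety conclusion is affected; the estimated effects on fitness, fat mass and cognition are not directly affected. Confidence is high on harms and moderate on dropout.

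**What to change.** Replace the sentence in section 3.5.4 so that:

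1. injuries, and illnesses leading to medical care or missed school, are recorded regardless of presumed cause, by the same short parent item in both arms at the June measurement;
2. the monitors' session log is kept as an additional source for the intervention arm;
3. the investigator judges relatedness;
4. adverse effects are added to the existing monthly contact with monitors;
5. the reason for missing the June measurement is recorded alike in both arms;
6. events are reported by randomised arm.

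The cost is one questionnaire item, one question in a contact that already takes place, and one descriptive table; parents already complete questionnaires on quality of life and eating habits. The drawbacks are that parents' recall over a school year is imperfect and that, as the Discussion acknowledges, parents are not blinded. The recall period is at least the same in both arms.

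The article describes the programme, run from October 2017 to May 2018, in the past tense, so collection may have closed. In that case, report harms as an uncontrolled, programme-attributed count in the intervention arm, draw no comparative safety conclusion, and state which dropout reasons are available in each arm. That costs a few sentences in the report.
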